### Sampling procedures

A random complex, multistage sampling of 9000 adolescents and adults aged 15.0–65.0 years, stratified by geographical location (only urban areas), gender, age and socioeconomic status was performed to select a representative sample of the urban household population of eight Latin American countries. Only urban areas were included in order to keep homogeneous population in the research, and based on the fact that almost all countries have at least 80–90 % of their population living in urban areas. Individual quotas were defined for each of these variables, which allow the identification of the total numbers of interviews required to properly represent the socio-demographic distribution under study. The survey was designed in order that no more than one subject were selected from a household.

The sampling size was calculated with a confidence level of 95 % and a maximum error of 3.49 %. A survey design effect of 1.75 was estimated based on guidance from the U.S. National Center for Health Statistics [27], and calculations of the minimum sample sizes required per strata (i.e., socioeconomic level (SEL), age, and gender) were performed for each country. Table 2 shows a detailed description of the case numbers required per strata in each of the 8 study sites.

**Table 2 Tab2:** Estimated distributions of country-specific samples according to age range, gender, and SEL

	Age range				Gender		SEL			Total sample size	Margin of error (%)
	15–19.9 years	20–34.9 years	35–49.9 years	50–65 years	Male	Female	High	Middle	Low		
Argentina	144	444	336	276	576	624	72	504	624	1200	2.83
Brazil	220	760	600	400	940	1060	520	940	540	2000	2.19
Chile	113	305	270	183	426	444	61	348	461	870	3.32
Colombia	148	443	357	283	615	615	62	357	812	1230	2.79
Costa Rica	111	300	229	150	395	395	87	450	253	790	3.49
Ecuador	128	312	224	136	400	400	104	576	120	800	3.46
Peru	165	440	308	187	528	572	209	374	517	1100	2.95
Venezuela	143	418	319	220	528	572	55	154	891	1100	2.95

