The demographic data were obtained from the appropriate national statistics institutes of each country. The selection of the households was design in four stages. In the first stage, total urban population was employed to define main regions proportionally in each country first, and then select cities representing each region - main cities and other cities representatives of the region, mixing a random method and sampling criteria, and trying to fulfill urban population coverage to the maximum possible. This mixed criterion enabled an increase in the efficiency of the fieldwork according to the study characteristics. In the second stage, sampling points (census tracts) of each city were randomly selected. In the third stage, a cluster of households was selected from each sampling unit. Addresses were chosen systematically using standard random route procedures, beginning with an initial address selected at random and selection of households with three systematic jumps, that is, the selection of a given household was made by randomly picking the first home and subsequently skipping 3 households. Finally, in the fourth stage, selection of respondent within a household was performed using two criteria: in each sampling unit, half of the households the participant was selected by the next birthday criteria; in the other half selection was by quotas of gender, age, and SEL.

The field interviewer arrived at the home, show an official identification badge, a letter introducing ELANs study, and briefly explain the survey’s purpose. A screener questionnaire to enumerate the household and to determine eligibility to participate further in ELANS was fulfilled. Thereafter, the selected participant signed the informed consent form.

A telephone number was available for the participants in order to answer any questions about the research, and use of the accelerometer device.

In the following circumstances - unsuccessful attempts to contact the target individual, total refusal to participate, obstruction by a family member, or inability to participate for a specified reason (e.g., travel, agenda, hospitalization) - substitutes were chosen in the home next door, following the same random selection criteria described above.

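### The Table 2 country margins of error, including the 3.49 % maximum, leave out the design effect of 1.75 stated beside them

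*Protocol article*

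**What the plan says.** Under Sampling procedures the protocol article states: "The sampling size was calculated with a confidence level of 95 % and a maximum error of 3.49" %. The next sentence adds: "A survey design effect of 1.75 was estimated based on guidance from the U.S. National Center for Health Statistics", and goes on to say that minimum sizes per stratum (socioeconomic level, age, gender) were calculated for each country.

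Table 2, titled "Estimated distributions of country-specific samples according to age range, gender, and SEL", gives a total sample size and a margin of error for each country. Its largest margin is 3.49 %, for Costa Rica with 790 participants, so the maximum in the text is the maximum of that column. Nothing in the text or table says that the margins exclude the design effect.

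The same section describes a multistage sample: cities within regions, then census tracts, and then "a cluster of households was selected from each sampling unit". The Analysis plan makes the primary outcome descriptive: the distributions of overweight, obesity, and energy intake and expenditure across countries and regions.

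**The concern.** A design effect above 1 widens the margin that a given sample size can deliver. If 1.75 belongs to the sample size calculation, it should be visible either in larger samples or in wider margins. The printed pairs of sample size and margin look like textbook values for simple random sampling, which would mean that 1.75 was quoted but never applied.

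These margins are the only numerical precision the article states for a study whose primary outcome is a description by country. A reader judging how finely countries can be described or compared would take them at face value and credit the study with more precision than its own planning assumption allows.

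**Working it through.** **Inputs.** From Sampling procedures: 95 % confidence (z = 1.96), maximum error 3.49 %, design effect 1.75. From Table 2: sample size and margin for each country. The article does not state the proportion p. I take p = 0.5, the worst case that a maximum error implies, and vary it below.

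**Formula.** Margin = 1.96 × √(D × p(1 − p)/n), where D is the design effect.

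**Step 1: reproduce the printed margins, then apply 1.75 (p = 0.5).** For Costa Rica, D = 1 gives 1.96 × √(0.25/790) = 3.487 %, printed as 3.49. Multiplying by √1.75 = 1.323 gives 4.61 %.

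| Country | n | Printed % | D = 1 | D = 1.75 |
|---|---|---|---|---|
| Argentina | 1200 | 2.83 | 2.829 | 3.74 |
| Brazil | 2000 | 2.19 | 2.191 | 2.90 |
| Chile | 870 | 3.32 | 3.322 | 4.40 |
| Colombia | 1230 | 2.79 | 2.794 | 3.70 |
| Costa Rica | 790 | 3.49 | 3.487 | 4.61 |
| Ecuador | 800 | 3.46 | 3.465 | 4.58 |
| Peru | 1100 | 2.95 | 2.955 | 3.91 |
| Venezuela | 1100 | 2.95 | 2.955 | 3.91 |

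All eight printed values agree with D = 1 to within 0.005 points. Solving the formula for D from each printed margin gives 0.997 to 1.002.

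**Step 2: could 1.75 be in the margins by another route?**
- *A smaller p.* With D = 1.75, the printed margins require p of about 0.172 in every country. The article names no such value, and it does not fit a maximum error.
- *90 % confidence.* With z = 1.645 and D = 1.75, Costa Rica would be 3.87 %, not 3.49 %, and the article states 95 %.

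**Step 3: sample size needed for 3.49 %.** Without a design effect: 1.96² × 0.25/0.0349² = 788.5, so 789, which is essentially Costa Rica's 790. With 1.75: 1.75 × 788.5 = 1,380 per country, which only Brazil reaches.

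**Step 4: dependence on p, with D = 1.75.**

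| p | Largest margin % (Costa Rica) | Countries above 3.49 % |
|---|---|---|
| 0.5 | 4.61 | 7 (all but Brazil) |
| 0.4 | 4.52 | 7 (all but Brazil) |
| 0.3 | 4.23 | 5 (Chile, Costa Rica, Ecuador, Peru, Venezuela) |
| 0.25 | 3.99 | 3 (Chile, Costa Rica, Ecuador) |
| 0.2 | 3.69 | 3 (Chile, Costa Rica, Ecuador) |

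The factor of 1.32 between adjusted and unadjusted margins is the same in every row, because p cancels.

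**The case against.** The strongest reply is that the design effect sentence runs on to the minimum sizes per stratum, while the 3.49 % stands in the sentence before it. On that reading, 1.75 was meant for the strata, and the margin column is an unlabelled simple-random-sampling figure. This softens the wording but does not rescue the numbers. The country margins would still ignore clustering in a clustered sample. Nor does Table 2 show strata inflated by 1.75: the counts are plain shares of the country total (Argentina by socioeconomic level 72 + 504 + 624 = 1200, by gender 576 + 624 = 1200; Brazil by socioeconomic level 520 + 940 + 540 = 2000).

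A second reply is that 4.61 % and the count of seven are worst-case figures. This stands. The Background puts obesity in Latin America at nearly a quarter of the population; at p = 0.25 only three countries exceed 3.49 %. The 1.75 is itself a planning estimate, and the realised design effect may differ. A margin for a proportion also says nothing about energy intake and expenditure, which the Analysis plan treats as continuous.

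A reader might go further and infer that the study's 95 % intervals will cover only about 86 % (2Φ(1.96/1.323) − 1 = 0.862). The article does not support that. It nowhere says that the Table 2 margins will serve as analysis intervals. The Analysis plan has multilevel models with region and country levels, and clustered standard errors for the structural equation models. The error lies in the stated planning precision, not in a described analysis.

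**Conclusion.** The point holds. The 3.49 % maximum error and all eight Table 2 margins are simple-random-sampling values, and they do not fit the design effect of 1.75 given in the same paragraph. On the plan's own figure, the margins should be 32 % larger at any p. In the worst case, p = 0.5, the maximum is 4.61 % instead of 3.49 %, and seven of eight countries exceed the stated maximum.

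The 32 % rests only on the article's 1.75. The 4.61 % and the count of seven also rest on p = 0.5, which the article does not state but which reproduces its printed margins. They describe the design-adjusted worst case, not the precision of every prevalence the study will report. No planned model or test depends on the 3.49 %, so this corrects the stated precision and does not invalidate the sample.

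**What to change.** Keep the sample sizes; the article says that fieldwork is ending.

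1. In Sampling procedures, restate the maximum error as 4.61 %, naming p = 0.5 and the design effect of 1.75.
2. In Table 2, replace the margin column with 3.74, 2.90, 4.40, 3.70, 4.61, 4.58, 3.91 and 3.91 % in the printed country order. Alternatively, label the present column as simple random sampling and add these values as a second column.
3. If country prevalences are reported with intervals, let these reflect the actual stages: cities, then census tracts, then households. The census tract should not be taken as the primary unit by default, because cities are selected before tracts and between-city variation would be lost.

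The cost is one sentence and one table column, with no extra participants. The stated precision becomes less favourable.

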**Methods/Design:**

The ELANS is a multicenter cross-sectional nutrition and health surveillance study of a nationally representative sample of urban populations from eight Latin American countries (Argentina, Brazil, Chile, Colombia, Costa Rica, Ecuador, Perú and Venezuela). A standard study protocol was designed to evaluate the nutritional intakes, physical activity levels, and anthropometric measurements of 9000 enrolled participants. The study was based on a complex, multistage sample design and the sample was stratified by gender, age (15 to 65 years old) and socioeconomic level. A small-scale pilot study was performed in each country to test the procedures and tools.

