Studies that combine nutrition and physical activity assessment in representative samples of Latin American countries are lacking. In this direction, the Latin American Study of Nutrition and Health/*Estudio Latinoamericano de Nutrición y Salud* (ELANS), which is randomized cross-sectional multicenter investigation of the nutritional and physical activity statuses of adolescents and adults in eight Latin American countries, was designed. The study aims to (1) provide up-to-date reliable and comparable data of dietary intake, physical activity, and its association with anthropometric profile among representative urban populations of eight Latin American countries; (2) measure variation in overweight, dietary intake and physical activity by region, cultural background, socioeconomic status, age and gender; (3) add new scientific-based evidence to describe the interplay among energy intake, energy expenditure, and anthropometric measurements. Our overarching hypothesis is that the relationships between dietary and physical activity profiles will differ across countries and across different environmental settings.

Up to now, there is no Latin American study using a central standard methodology across a group of participating countries. Previous multicenter studies [23–26] were important references to determine the rationale and design of ELANS.

The purpose of this report is to describe the design and methodology of the ELANS. The study is currently ending the fieldwork data collection.

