As exclusion criteria were considered pregnant and lactating women (in the first 6 months postpartum), individuals with major physical or mental impairments that affect food intake and physical activity (e.g., musculoskeletal disease, recent surgery, severe asthma, dementia, major depression), individuals below 15 or over 65 years old, adolescents without assent and consent of a parent or legal guardian, individuals living in any residential setting other than a household (e.g., hospitals, regiments, and nursing homes), and individuals unable to read.

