### Dietary assessment

The 24-h method was selected because of its nearly universal applicability across populations with varying literacy skills and its relatively low burden for participants [28]. Each recall was conducted using the Multiple Pass Method [29] and ascertained all foods, nonalcoholic and alcoholic beverages, water and dietary supplements consumed over the prior 24 h in depth. The BEVQ was designed to obtain the frequency of beverage intake across 10 beverage categories (water, flavored water, soft drinks, fruit drinks, sport drinks, energy drinks, tea and coffee drinks, other non-alcoholic drinks, and alcoholic drinks). For each beverage, participants answered whether they consume the specific category of beverage, the frequency of intake (daily, weekly, monthly), and how often they drink the beverage during the selected unit (1–10 occasions). The list of beverages included in the questionnaire was standardized as much as possible across the ELANS countries; however, regional variations in beverage consumption patterns required some cultural and regional adaptations for some items within beverage categories.

The food and beverages intakes recorded with the 24-h is transformed into energy, macronutrients and micronutrients values using the Nutrition Data System for Research version 2013 software (NDS-R, University of Minnesota, MN). A food matching standardized procedure involving nutritional equivalency of local food items reported by the study participants into foods available in NDS-R database was strictly conducted by each country, and describe in detail elsewhere [30]. A concordance rate of at least 80 % to 120 % for energy and macronutrient content was required to establish a nutritional equivalency of local food items to foods available in NDS-R database.

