### Analysis plan

The primary outcome of interest will be to describe the distributions of overweight and obesity, and energy intake and expenditure intake across the countries and regions of the study. A secondary objective of the study will be to identify the individual characteristics associated with the two main outcomes of interest (obesity and energy intake/expenditure) and to test whether these associations vary across the different regions by applying the statistical methodologies described below. These individual characteristics of interest will include, but are not be limited to, education, marital status, age, sex and individual income. The results of the three main outcomes will also be presented after stratification for each of the individual characteristics.

Initially, basic statistical models will be applied to analyze the aggregated results for all the individuals in the multicenter study to identify the individual characteristics (independent of area of residence) associated with each of the outcomes, with the inclusion of all the projected 9000 individuals. Separate individual models for each of the countries will also be performed.

We will also test the presence of statistically significant differences between regions of residence and countries by adjusting multilevel models (also known as hierarquical linear models), where the individual results will be included as the first level of the model and the region of residence as the second level of the model. Overweight and obesity will be analyzed separately as dichotomous dependent variables (vs. normal weight) by adjusting logistic multilevel models, while energy intake and expenditure will be treated as continuous dependent variables and multilevel linear models will be adjusted. We will test for a statistical difference of the dependent variables according to region of residence (a two-level model) and also by including the country of residence as the third level of the previous multilevel models. Statistical difference between the regions and the countries will be tested by analyzing the area-level variance (between-group variation) of each multilevel model.

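### People unable to read are excluded without a stated reason, yet the sample is called representative of the urban population with no literacy limit

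*Protocol article*

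**What the plan says.** The exclusion criteria under Sampling procedures end with "and individuals unable to read". No reason is given.

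Three places describe whom the sample represents, none with a literacy limit:

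- Abstract, Methods/Design: "nationally representative sample of urban populations from eight Latin American countries".
- Background, aim 1: "among representative urban populations of eight Latin American countries".
- Sampling procedures: "to select a representative sample of the urban household population of eight Latin American countries".

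Aim 2 in the Background is to "measure variation in overweight, dietary intake and physical activity by region, cultural background, socioeconomic status, age and gender". The Analysis plan names the individual characteristics of interest as including, "but are not be limited to, education, marital status, age, sex and individual income", and says the main outcomes will also be presented by each of them.

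Dietary assessment explains the choice of the 24-h recall by "its nearly universal applicability across populations with varying literacy skills and its relatively low burden for participants". Two kinds of step do involve reading or writing: the signed consent form (Sampling procedures), and the written instructions and self-completed log for the 40 % who wear an accelerometer (Objectively assessed activity).

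The Discussion lists weaknesses. On generalizability it warns only about other countries; people unable to read are not mentioned.

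**The concern.** A person unable to read has no chance of selection, so the sample cannot represent the urban household population as a whole. Nothing later in the design restores the missing group. Quotas are set on gender, age and SEL, using demographic data from national statistics institutes, and no literacy adjustment is described. A low-SEL or 50-65 quota can be filled entirely with readers and still look complete.

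At stake are stated results: variation by SEL and age, and the association of education with obesity and energy intake or expenditure. Inability to read is closely tied to little schooling, so the exclusion probably removes part of the low end of the education range. If the share unable to read differs between countries, cross-country contrasts are affected too. The documents give no data on how non-readers are spread over age, SEL or country, so that pattern is plausible but assumed.

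**Working it through.** **1. The plan's own margins.** With p = 0.5, simple random sampling and 95 % confidence, margin = 1.96 × √(0.25/n). Table 2 is reproduced to two decimals:

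| Country | n | Stated (%) | Recomputed (%) |
|---|---|---|---|
| Argentina | 1200 | 2.83 | 2.83 |
| Brazil | 2000 | 2.19 | 2.19 |
| Chile | 870 | 3.32 | 3.32 |
| Colombia | 1230 | 2.79 | 2.79 |
| Costa Rica | 790 | 3.49 | 3.49 |
| Ecuador | 800 | 3.46 | 3.46 |
| Peru | 1100 | 2.95 | 2.95 |
| Venezuela | 1100 | 2.95 | 2.95 |

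These margins express sampling error only. The exclusion does not enter them.

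**2. Bias formula.** Let W be the share of the target population unable to read and D the difference in prevalence between non-readers and readers. An estimate from readers alone differs from the full-population value by W × D. Sample size does not appear in it.

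**3. Assumed inputs.** The documents give neither W nor D. Results in percentage points:

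| W | D = 5 | D = 10 | D = 15 |
|---|---|---|---|
| 2 % | 0.10 | 0.20 | 0.30 |
| 5 % | 0.25 | 0.50 | 0.75 |
| 10 % | 0.50 | 1.00 | 1.50 |
| 20 % (an older or low-SEL stratum) | 1.00 | 2.00 | 3.00 |

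**4. The matching yardstick.** A stratum bias belongs against the precision of that stratum. From the Table 2 counts, with the formula of step 1:

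| Estimate | n | Margin (points) |
|---|---|---|
| Ecuador, low SEL | 120 | 8.9 |
| Ecuador, ages 50-65 | 136 | 8.4 |
| Costa Rica, ages 50-65 | 150 | 8.0 |
| Venezuela, low SEL (largest low-SEL stratum) | 891 | 3.3 |
| All countries, ages 50-65 | 1835 | 2.3 |
| All countries, total | 9000 | 1.0 |

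The pooled 50-65 count is 276 + 400 + 183 + 283 + 150 + 136 + 187 + 220 = 1835. Applying the stated design effect multiplies each margin by √1.75 = 1.32, so the two pooled margins become 3.0 and 1.4 points.

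**5. Comparison.** The overall bias of 0.1-1.5 points is below every stated national margin. A bias of 1-3 points is well under half the margin in the smaller country strata and comes near it only in the largest. Against the pooled estimates, the upper end of the assumed range reaches the margin: 1.5 against 1.0 (1.4 with the design effect) overall, and 3.0 against 2.3 (3.0) for ages 50-65.

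**The case against.** The exclusion is disclosed in the very section that makes the claim, so a careful reader can work out the population. Other exclusions (pregnancy, impairments affecting intake or activity, minors without consent) also narrow it without a change to the word representative. Reading had a use for consent and for the accelerometer log, and one eligibility rule allows the 40 % subsample to be drawn from all participants. The likely bias is small beside country-level sampling error.

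Much of this stands. The exclusion is not hidden, it may have had a practical purpose, and its numerical effect on national figures may be minor. But disclosure does not make an unqualified claim true. The health, pregnancy and residence exclusions have an evident link to the outcomes or to the household frame, whereas no reason is given for this one. Weight and height, which give the overweight and obesity outcomes, need no reading.

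Three stronger readings are tempting and are not supported:

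- *That the exclusion contradicts the reason for choosing the recall.* The phrase "nearly universal applicability across populations with varying literacy skills" can describe people who read at different levels. The two statements are in tension only.
- *That excluded people were replaced by neighbouring households.* The substitution triggers are failed contact, refusal, obstruction by a family member, and inability to take part for reasons such as travel or hospitalization. Ineligibility is not listed, and another member of the same household might have been chosen. The point rests on the quotas, not on substitution.
- *That a 1-3 point bias in an older or low-SEL stratum rivals the stated precision.* That sets a stratum bias against national margins; the country stratum margins are mostly much wider.

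**Conclusion.** The point holds as a mismatch between the claimed and the sampled population. Eligibility limits the study to people able to read, while the abstract, the aims and the sampling section claim the urban population without that limit, and the limitations do not correct it. This affects most directly the planned results by SEL, age and education.

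The size cannot be derived from the documents. All inputs to the 0.1-1.5 point overall figure and the 1-3 point stratum figure are assumed, including any concentration of non-readers in older or low-SEL groups. On those assumptions the bias is minor for single-country estimates. It is not negligible for pooled ones, because it stays fixed while the margin narrows. The pooled comparison further assumes that the shares at the upper end apply across all eight countries together.

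**What to change.** - In the abstract, the aims and the sampling section, state the target population as urban household residents aged 15-65 who are able to read.
- Add the exclusion to the limitations in the Discussion.
- Confine conclusions about low SEL, low education and differences between countries to that population.
- Report the number excluded for inability to read by country, and by age, if the screener recorded it. The article says only that the screener enumerated the household and determined eligibility. It does not say that the reason for exclusion was kept, and the SEL questionnaire is part of the first visit to the selected respondent, so a breakdown by SEL may not exist.

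The first three changes need wording only and remain possible with fieldwork ending. The count depends on what was recorded and belongs in the results report. The price is a narrower claim.
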